### Plans to give access to the full protocol, participant level-data and statistical code {31c}

This protocol is planned for publication in an open access journal. We plan to publish the statistical code for the primary and secondary outcome analyses as a supplement to the main manuscript publication. Participant-level data can be accessed from the corresponding author on reasonable request.

## Oversight and monitoring

### Composition of the coordinating centre and trial steering committee {5d}

The trial steering committee (SC) consists of the principal investigator (OL) and the co-principal investigator (JT) who will meet in-person or via video link at least on a monthly basis. They are responsible for overseeing the trial and disseminating any changes. At each site, a small team of physician will be instructed and given access to the protocol, study flow chart and the eCRF so that they can recruit patients. They will receive at least one introductory trial-specific education by a member of the protocol author group on site or via video link. The SC will also be available via e-mail, work phone number or video link for questions from the locally responsible trial physician at any of the sites, on a day-to-day basis if needed. On-site responsible physician will receive study updates at least every 6 months. The primary outcome assessor will have access to the SC on a weekly basis.

### Composition of the data safety and monitoring committee, its role and reporting structure {21a}

The Data Monitoring Committee (DMC) will consist of three physician scientists and one biostatistician. [name] will lead the DMC. He has extensive experience with running RCTs and is a professor and consultant in intensive care. [name], specialist in infectious disease, and [name] and specialist in clinical microbiology, will also be members of the DMC. The investigators are jointly responsible with the DMC for safeguarding the interests of participating patients and for the conduct of the trial. The DMC will be advisory to the trial investigators regarding the safety and efficacy of the trial. The DMC will be responsible to make a recommendation from blinded data at the interim analysis regarding safety and futility (see above). They will also be informed about serious adverse events (SAE) reported by the trial investigators on a half year basis but can request additional monitoring for SAE at any time. The DMC will meet live at least once for the interim analysis and are recommended to have online meetings at least every half year when SAE reports are delivered. The DMC can request unblinding from the SC if they believe that it is needed to make a valid recommendation.

### Adverse event reporting and harms [22]

Because the trial evaluates well-known and well-used drugs, we have an agreement with the Swedish Medical Products Agency to primarily focus on severe adverse events (SAE, see definition in Table 4 below). The recruiting trial physician will have the primary responsibility to identify and report any SAE from allocation and until day 28. If the telephone interviewer suspects an SAE, they are required to contact the recruiting physician by telephone the same day. If the recruiting physician identifies an SAE, then he or she is required to email the investigators as soon as possible or at latest within 24 h. If a connection between the SAE and the study drug cannot be ruled out, the investigators are responsible to report to the sponsor within 24 h. The sponsor is responsible for ensuring that a serious unwanted and unexpected incident or reaction, which is suspected to be related to the study drug (SUSAR = suspected unexpected serious adverse reaction) is reported to the Medical Products Agency ([contact]) on a CIOMS form. SUSARs that are life-threatening or fatal are reported within 7 days to the Medical Products Agency and the Ethical Review Board, and other SUSARs are reported within 15 days. In this study, the Medical Products Agency registers SUSAR in the European trial module EudraVigilance. As long as the trial is ongoing, a safety report will be compiled once a year and reported via EudraCT to the Medical Products Agency.

**Table 4 Tab4:** Definition of adverse events

Intensity of incident	• Mild does not affect the patient's normal functions • Moderate affects the patient's normal functions to some extent • Severe affects the patient's normal functions to a great extent
Assessment of the connection between incident and study drugs	• Not (unlikely) related to the study drug: there is very little or no possibility that the study drug has caused the unwanted event. • Possibly related to the study drug: the association between the adverse event and the study drug is unknown but there is no other clear cause for the symptoms. • Probably related to the study drug: a reasonable temporal relationship exists between the adverse event and the study drug. Based on the investigator's clinical experience, the association is considered probable.
Serious adverse event	Definition: Any incident or reaction that results in • deaths • is life threatening • requires hospital care or extends an already started care session in hospital • causes a permanent or significant disability or disability • constitutes a congenital malformation or congenital defect.

Recruiting physicians are also encouraged to report non-serious incidents in a specific AE form in the eCRF at any time during hospitalisation or during the retrospective chart review. An incident (adverse event) is defined as any adverse medical event in a patient who has received a study drug. Non-serious incidents are further divided into mild, moderate or severe (as defined below). Relationship between incident and study drug are defined unlikely, possible or probable, as defined below. Incidents that are judged to be related to the study drug will be followed up to enable an assessment of reversibility.

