Ciprofloxacin	Cyclosporine	Increase in serum creatinine
Ciprofloxacin	Vitamin K-antagonists	Increase in anticoagulant effect. Monitor INR.
Trimetoprim–sulfamethoxazole	Dofetilid, Amantadine, Digoxin, Memantine, Metformin, Methotrexate, Lamivudine, Paclitaxel, Amiodarone, Dapsone, Repaglinide, Rosiglitazone, Pioglitazone, Coumarins, Phenytoin. Sulfonylurea derivatives	Increased serum concentration of co-medication. Consider therapeutic drug monitoring.
Trimetoprim–sulfamethoxazole	Clozapine	Risk of agranulocytosis
Trimetoprim–sulfamethoxazole	Ciclosporin, Tacrolimus	Risk of decreased kidney function in kidney transplanted patients
Trimetoprim–sulfamethoxazole	Zidovudine, Azathioprine, Mercaptopurine	Risk of haematological dysfunction
Trimetoprim–sulfamethoxazole	ACE-inhibitors, Angiotensin receptor blockers, Potassium saving diuretics, Prednisolone	Risk of hyperkalaemia
Trimetoprim–sulfamethoxazole	Thiazides	Risk of thrombocytopenia
Trimetoprim–sulfamethoxazole	Tricyclic antidepressants	Decreased concentration of co-medication
Trimetoprim–sulfamethoxazole	Pyrimethamine	Risk of anaemia
Ertapenem	Valproate/Valproic acid	Decreased concentration of co-medication

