#### Secondary outcomes

Participants’ perception of treatment tolerability on a 1–10 scale.Early study drug discontinuation.Additional antibiotic subscriptions (for UTI) within 28 days from randomisation.Proportion of patients re-admitted to hospital (due to UTI symptoms) within 28 days from randomisation.Drug-related serious adverse events within 28 days from randomisation.All-cause mortality within 28 days from randomisation.Growth of EPE (phenotypically same species) in urine culture (10^3^ CFU/mL) 10 +/− 2 days after antibiotic treatment.Growth of EPE or carbapenemase-producing bacteria in faecal cultures 10 +/− 2 days after antibiotic treatment.

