### Procedure for unblinding if needed {17b}

Because care providers and patients are not blinded, there is no reason to unblind for safety of care. The Data Monitoring Committee (DMC) will be able to unblind the database if there are clearly more reports of possibly or probably study drug-related serious adverse events than expected.

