### Interim analyses {21b}

An interim analysis will be performed once half of the patients have been included (*n* = 165). Blinded data will be delivered by an independent statistician to the Data Monitoring Committee (DMC) who will then provide an allocation-blinded recommendation to the trial investigators whether to continue, hold or terminate the trial prematurely. The recommendation is based on safety and futility. Safety is based on three parameters, the number of possibly related serious adverse events, the number of early study drug discontinuations and the number of deaths within 28 days. It is difficult to provide fixed stopping criteria for safety since these events are expected to be very few, and the DMC have to assess frequency, severity and possible relationship to the study drug and give their best advice accordingly. Futility is defined as less than 5% probability of finding non-inferiority in the final analysis based on conditional power simulations as suggested by Bratton et al. [48]. The trial investigators will make the final decision whether to terminate the trial and will have to provide a written account to explain if they do not follow the recommendation from the DMC.

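### Table 4's three relatedness grades leave a gap: an SAE with an uncertain drug contribution and another clear cause fits none of them, yet the grades feed secondary outcome 5 and the interim safety count

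*Protocol article*

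**What the plan says.** The relatedness scale is in Table 4, under Adverse event reporting and harms. The text after the table confirms that there are three grades and no others.

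- *Not (unlikely) related*: "there is very little or no possibility that the study drug has caused the unwanted event".
- *Possibly related*: "the association between the adverse event and the study drug is unknown but there is no other clear cause for the symptoms".
- *Probably related*: "a reasonable temporal relationship exists between the adverse event and the study drug", and the investigator, from clinical experience, considers the association probable.

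Relatedness is used in four places, each worded differently.

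- Secondary outcome 5: "Drug-related serious adverse events within 28 days from randomisation". The article does not say which grades count as drug-related.
- Interim analyses, first of three safety parameters: "the number of possibly related serious adverse events".
- Procedure for unblinding: the DMC may unblind if there are clearly more "possibly or probably study drug-related serious adverse events than expected".
- Reporting by the investigators to the sponsor: "If a connection between the SAE and the study drug cannot be ruled out".

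Under Who will be blinded, the treating physician who assesses secondary endpoints 2 to 8 is stated not to be blinded. That range includes secondary outcome 5.

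**The concern.** A causality scale that feeds a between-arm comparison should give every event exactly one place. Here *possibly related* excludes any event with another clear cause, while *unlikely* is reserved for events with next to no chance of a drug role. Nothing covers the ground between them when the drug role is uncertain and a competing cause is evident.

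Such events are foreseeable in this trial. Every participant has an acute febrile infection and has already had 1 to 5 days of intravenous antibiotics. Concomitant care is unrestricted. Table 2 lists effects to which study drug and co-medication both contribute, such as "Risk of hyperkalaemia" when trimethoprim–sulfamethoxazole is given with ACE inhibitors.

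At stake is the consistency of secondary outcome 5 and of one interim safety parameter. The Interim analyses section itself expects very few safety events, so one or two SAEs graded differently could change how the comparison looks. The choice for an event that fits no grade is left to a physician who knows the allocation.

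**Working it through.** The protocol gives no SAE rate and the point depends on no formula, so this is a check of logic. Take an SAE for which another clear cause is present, for example the infection or an interacting co-medication. Vary the strength of the suspected drug role and apply each Table 4 definition.

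| Drug role, another clear cause present | *Unlikely*: next to no possibility of a drug cause | *Possibly*: association unknown and no other clear cause | *Probably*: reasonable timing and association judged probable | Result |
|---|---|---|---|---|
| (a) Judged probable | Not met | Not met | Met | Graded as related |
| (b) Plausible but uncertain | Not met | Not met, another clear cause exists | Not met, not judged probable | No grade fits |
| (c) Negligible | Met | Not met | Not met | Graded as unrelated |

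The gap is row (b) only. Following a row (b) event through the places where relatedness is used:

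1. **Sponsor reporting.** A link cannot be ruled out, so the event is reported.
2. **Secondary outcome 5.** The event has no grade, and the outcome does not say which grades count. The assessor may file it as unlikely (not counted), stretch *possibly* (counted) or stretch *probably* (counted).
3. **Interim safety count.** As written, the event does not meet *possibly related*, so it is not counted.
4. **DMC unblinding provision.** As written, the event is neither possibly nor probably related.

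The same SAE can thus be reported to the sponsor as not ruled out and still be absent from the comparison between arms.

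There is also a smaller mismatch. Read literally, the interim parameter names only *possibly related* SAEs, so a row (a) event would not be counted there. The unblinding provision names both possible and probable.

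The frequency of row (b) events cannot be derived from the document.

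**The case against.** The strongest points on the other side are these.

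- **Jointly caused events are not shut out.** *Probably related* does not require the absence of another cause. When potassium or INR rises after a listed drug is started, the study drug is the new element and a physician can well judge the association probable. This stands, and it confines the gap to row (b). A reader might infer that all SAEs caused jointly by drug and co-medication or infection are left out; the text does not support that. Nor does it say that ungraded events are excluded. It leaves them undefined.
- **No direction of bias is established.** A reader might infer that control-arm counts fall more, because Table 2 has 14 interaction rows for control drugs (trimethoprim–sulfamethoxazole 8, ciprofloxacin 5, ertapenem 1) and 7 for the intervention. But a control patient receives one drug and an intervention patient receives both components. At the shares expected in Table 1, a control patient meets 0.35 × 8 + 0.25 × 5 + 0.40 × 1 = 4.45 rows on average, against 7. Neither count measures SAE frequency.
- **The interim review is not a mechanical count.** There is no fixed safety stopping rule, and the DMC weighs relationship to the drug itself. Deaths and early discontinuations are counted without a causality filter. The DMC receives SAE reports every half year and may ask for more. This stands and limits the interim consequence, but it does not repair secondary outcome 5.
- **A reporting trigger wider than the analysed outcome is cautious.** This also stands. The trigger itself is not at fault; the problem is that an event it catches has no grade. Reading the interim wording as at least possibly related is natural, but one added word removes the doubt.
- **The secondary objectives are declared exploratory.** This is correct, and it keeps the point modest.

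**Conclusion.** The point holds in a narrow form. Table 4's grades are not exhaustive: an SAE with a plausible but uncertain drug contribution and another clear cause meets no definition. As written, such events can be missed by, or inconsistently assigned to, secondary outcome 5 and the interim count, although they are reported to the sponsor. This is a defect in a stated rule, not a detail left to an analysis plan.

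Its size is unknown. The document supports no estimate of how many SAEs are affected and no claim that one arm is favoured. Because the grading physician is unblinded, misclassification could differ by arm in either direction. The primary outcome, the sample size and the non-inferiority conclusion are untouched. The conclusion assumes that the definitions are applied as printed and that the eCRF or its instructions, which are not shown, do not already close the gap. The correction is worth making because it is specific and costs almost nothing.

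**What to change.** 1. In Table 4, define *possibly related* as a reasonable possibility that the study drug caused or contributed to the event, whether or not another cause is present.
2. Define *drug-related* once, as possibly or probably related, and use that definition in secondary outcome 5.
3. In Interim analyses, change the first safety parameter to possibly or probably related SAEs, which matches the unblinding provision.
4. Keep the sponsor-reporting trigger at least as wide as this definition.

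The cost is a few changed phrases and a short instruction to the grading physicians. The downside is small: related-SAE counts may rise slightly in both arms. SAEs graded before the change should be checked once against the new wording, so that one definition applies throughout.

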### Frequency and plans for auditing trial conduct [23]

Clinical Trials Sweden—Forum South will monitor the trial with a risk-based approach in accordance with ICH GCP E6(R2). The monitoring purpose is to safeguard the study participants rights and well-being, the validity and completeness of study data collection and to ensure that the study conduct is in accordance with the protocol and ethical and regulatory demands. Monitors will have a live or web-based start-up meeting with each participating site before the study is initiated and conduct two monitor visits during the 3–4 years of patient recruitment for the trial. The first visit will be after 2–5 participants have been recruited and the second visit after 10 additional participants have been recruited, or after 1 year if less than 10 participants have been recruited. The primary monitoring focus will be on informed consent, adverse events reporting and consistency of data entry into the eCRF. The monitor will remind recruiting physician to do the retrospective review. If the monitor discovers major deviations from the protocol, further monitoring visits will be planned. Clinical Trials Sweden—Forum South is a collaboration between Sweden's six healthcare regions (including the sponsor) and is supported and funded by the Swedish Research Council and is independent from the trial investigators. The study will be performed in compliance with the study protocol, the Declaration of Helsinki, ICH-GCP (Good Clinical Practice) guidelines and current national and international regulations governing this clinical trial. In case of an inspection or an audit, the investigator will give direct access to source data in the trial to representatives of the regulatory authority (in case of an inspection) and to the representatives of the sponsor (in case of an audit).

### Plans for communicating important protocol amendments to relevant parties (e.g. trial participants, ethical committees) {25}

The steering committee are responsible for disseminating any important protocol modifications to the ethical board, the Medical Products Agency, the monitoring agent, locally responsible physicians and trial participants in accordance with which party is affected. Extensive changes or safety concerns will be communicated directly by phone and moderate changes by e-mail within 1 week. If there are no changes and the trial runs as planned, we will update site responsible physicians in the least every 6 months. All trial updates will also be posted on the trial-specific homepage www.pacuti.se
.

### Dissemination plans {31a}

We plan to publish the trial results in a peer-reviewed medical journal.

## Discussion

### Methodology

Choosing a non-inferiority design always constitutes a compromise in scientific validity compared to a placebo-controlled superiority trial. However, giving patients with serious infections placebo is not ethical, and because EPE-causing febrile UTI is (yet) uncommon in Sweden, we considered a non-inferiority trial to be the best compromise. This enables a high possibility for completing the trial with our available resources and within a reasonable timeframe. The implementation of a surveillance system for EPE in urine and blood cultures in Swedish microbiology departments should be an effective method to ensure consistent recruitment.

Preferably, the treating and recruiting physician and other healthcare personnel would be blinded to treatment allocation. With our design, using three oral and one intravenous antimicrobial, with one to three doses daily, it was overwhelming to us, both in complexity and cost, to design a completely blinded intervention. This non-blinding may affect how patients are treated and how the protocol is adhered. Part of this bias may be managed by analysing the primary outcome both as ITT, mITT and PP. We have put efforts into keeping the primary outcome assessor blinded and stringent in their assessment through the use of a few trained centralised assessors using a study-specific structured interview.

We have chosen to evaluate microbiological cure as a secondary outcome and not include it in the composite clinical cure outcome in contrast to a recently published comparable trial [50]. This choice was not an obvious one. Including microbiological eradication in the composite outcome could increase the objective aspect of a chiefly subjective outcome. We concluded however that mixing clinical cure and microbiological cure could introduce a risk of inaccuracy towards what we are really looking to evaluate, i.e. whether the patient is alive and well. Microbiological eradication is intuitively desirable but in lack of clinical symptoms of UTI empirical data from studies of asymptomatic bacteriuria (ASB) paint a different picture. These tell us that short-term microbiological resolution is often not sustained [51] and that ASB is not necessarily a predictor of symptomatic urinary tract infection (UTI) [52] and may even be protective [53]. Furthermore, follow-up urine cultures are outside of routine management for UTIs in Sweden and we would like the primary outcome to be pragmatic and mirror clinical practice. Any substantial discrepancy between clinical cure and microbiological cure between intervention and control will warrant further investigation, however.

### Benefit versus harm

We consider there to be a low risk of harm from participating in this trial since all drug-specific medications are well-known and widely used. The major risk from a patient perspective is if the intervention is inferior to control. We try to minimise this potential for harm through an interim analysis once half of the intended population has been randomised.

If this trial can show non-inferiority, the potential benefit is the addition of another safe, well-tolerated treatment alternative in the era of antimicrobial resistance. This could, in the best of worlds, improve patient autonomy, lower health-care costs and decrease the drive for further resistance.

## Trial status

Protocol version 1.0 (1 December 2020): first protocol draft

Protocol version 2.0 (21 January 2021): lightly revised protocol sent for ethical and Swedish Medicine Agency approval

Protocol version 3.0 (10 Sept 2021): major protocol revision to fit Trials journal guidelines and sample size update to 330 participants

Protocol version 4.0 (5 May 2022): references update and changed responsibilities of trial statistician

Protocol version 5.0 (30 Sept 2022): major changes in primary outcome evaluation from live visit to centralised telephone interview and addition of third alternative (ertapenem) in control group

Protocol version 5.1 (7 Oct 2022): updates on funding and microbiological sampling

Protocol version 5.2 (27 Oct 2022): updates on DMC responsibilities

Protocol version 5.3 (15 Nov 2022): update on endpoint definition and outcome assessment if discordance

Protocol version 6.1-6.2 (15 Dec 2022): update on adverse events and interactions by request from the Swedish Medical Products Agency

Protocol version 6.3 (31 Jan 2023): updated background with PAC rationale

Protocol version 6.4 (27 Feb 2023): final revision after comments by co-authors

Protocol version 6.5 (13 July 2023, current): minor revision at *Trials* journal regarding SPIRIT item 32, reference checking and an elaboration regarding the choice not to include microbiological cure in the primary composite outcome and a clarification that the statistical analysis is between two groups even though the control group comprises three different drugs.

The first study participant was recruited on 19 April 2023 and recruitment is expected to be completed in year 2026.

